## Abstract

**Background:**

Giant congenital melanocytic nevi (GCMNs) are large brown to black skin lesions that appear at birth and are associated with a risk of malignant transformation. It is often difficult to reconstruct large full-thickness skin defects after the removal of GCMNs.

**Objective:**

To overcome this difficulty we developed a novel treatment to inactivate nevus tissue and reconstruct the skin defect using the nevus tissue itself. For this research, we designed an exploratory clinical study to investigate the safety and efficacy of a novel treatment combining the engraftment of autologous nevus tissue inactivated by high hydrostatic pressurization with a cultured epidermal autograft (CEA).

**Methods:**

Patients with congenital melanocytic nevi that were not expected to be closed by primary closure will be recruited for the present study. The target number of nevi is 10. The full-thickness nevus of the target is removed and pressurized at 200 MPa for 10 minutes. The pressurized and inactivated nevus is sutured to the original site. A small section of the patient’s normal skin is taken from around the nevus region and a CEA is prepared after a 3-week culturing process. The CEA is then grafted onto the engrafted inactivated nevus at four weeks after its retransplantation. The primary endpoint is the engraftment of the CEA at 8 weeks after its transplantation and is defined as being engrafted when the engraftment area of the inactivated nevus is 60% or more of the pretransplantation nevus area and when 80% or more of the transplanted inactivated nevus is epithelialized.

**Results:**

The study protocol was approved by the Institutional Review Board of Kansai Medical University (No. 1520-2, January 5, 2016: version 1.3). The study opened for recruitment in February 2016.

**Conclusions:**

This protocol is designed to show feasibility in delivering a novel treatment combining the engraftment of inactivated autologous nevus tissue and CEA. This is the first-in-man clinical trial of this treatment, and it should be a promising treatment of patients suffering from GCMN.

**Trial Registration:**

University Hospital Medical Information Network: UMIN000020732; https://upload.umin.ac.jp/cgi-open-bin/ctr_e/ctr_view.cgi?recptno=R000022198 (Archived by WebCite at http://www.webcitation.org/6jLZH2vDN)

## Introduction

Giant congenital melanocytic nevi (GCMNs) are large brown to black skin lesions that appear at birth and have a diameter of more than 20 cm [1-5]. GCMNs, which are reported to occur in approximately 1 in 20,000 newborns [1,2], are associated with a risk of transformation that usually results in malignant melanoma. The incidence of malignant transformation into malignant melanoma is reported to be 0.7% to 8.2% [2,5,6]. Histologically, nevus cells are present throughout the entire layer of the dermis and, in some cases, the subcutaneous tissue. Thus, the removal of the full thickness of the nevus tissue is necessary to remove nevus cells completely and to prevent the emergence of melanoma [1-5]. It is often difficult to reconstruct large full-thickness skin defects after the removal of GCMNs. It is also reported that melanoma and aneurocutaneous melanocytosis are most likely in patients with GCMNs that have a final size of more than 40 cm in diameter with numerous satellite nevi [6]. Thus, the skin reconstruction of GCMNs remains a challenge in the field of plastic and reconstructive surgery.

We have already reported that all cells existing in the human skin, porcine skin, and nevus tissue were inactivated completely after high hydrostatic pressurization (HHP) at pressures of more than 200 MPa [7,8]. We also reported that the human-cultured epidermis took and survived on the pressurized skin and nevus after pressurization at 200 MPa [7,9]. Skin consists of the epidermis, which acts as a barrier against infection and water loss, and the dermis, which supports and supplies nutrition to the epidermis. Regarding skin reconstruction, the regeneration of the epidermis by a cultured epidermal autograft (CEA) using Green’s method was established in the 1970s [10]. A method of dermal regeneration that achieves sufficient strength and elasticity has not yet been established [11,12].

We designed an exploratory clinical study to investigate the safety and efficacy of a novel treatment combining autologous nevus tissue inactivated by HHP and a CEA. This trial is the first-in-man clinical trial to reuse and apply autologous nevus inactivated by HHP to reconstruct autologous dermis after the removal of the nevus itself without discarding the nevus tissue. JACE (Japan Tissue Engineering Co Ltd, Gamagori, Japan) is a CEA product prepared using Green’s method that has been approved for use in Japan since 2007 [13]; CEA products are approved for use in other countries as well. A CEA of sufficient size to cover the total surface area can be produced from an autologous skin specimen of approximately 1 cm × 2 cm in size. This treatment can therefore be expected to overcome the issues of GCMN treatment and prevent the malignant transformation of GCMNs.

## Methods

### Primary Objective

The objective of this study is to evaluate the safety and efficacy of a novel treatment combining autologous nevus tissue inactivated by HHP with CEA.

### Design

This study is an open-label, nonrandomized, single-arm, controlled clinical trial that is a prospective study using historical data as a control. All of the patients will receive a combination treatment consisting of autologous nevus tissue inactivated by HHP with CEA.

The take rate of the CEAs implanted on the inactivated nevus tissue will be estimated at 8 weeks after CEA implantation and compared to the historical data of the take rate of CEAs. This comparison will provide useful information for designing and conducting future trials.

### Setting and Participants

Patients with congenital melanocytic nevi will be identified by physicians in Osaka and other prefectures who will refer them to this study, being conducted at Kansai Medical University Hirakata Hospital.

Patients 7 months of age and older who are able to undergo surgery under general or local anesthesia and can give informed consent (proxy consent permitted for pediatric patients only) are included. Patients must have a congenital melanocytic nevi that is not expected to be closed by primary closure (patients require a skin graft or skin flap surgery to close the skin defect after its removal) with a target pigmented nevus area of 0.25% or more of the total body surface area (1/4 of the palmar area, including the fingers, taking the palm including the fingers as 1% of the total body surface area).

Exclusion criteria are extensive scarring from previous therapies (in whom the engraftment of the inactivated nevus is not expected), previous treatment of the target site by CEA in other clinical studies, history of malignant tumors with a disease-free interval of 5 years or less, two previous protocol treatments from this study, or patients who are judged by the investigator or subinvestigator to be inappropriate as study subjects.

### Interventions

#### Removal of the Target Nevus and Its Inactivation by HHP

The full thickness nevus of the target is removed under general or local anesthesia and the subcutaneous adipose tissue is removed by scissors and packed into a polyethylene bag filled with normal saline solution (Otsuka Pharmaceutical Co Ltd, Tokyo, Japan) and sealed. We use a portable HHP device that was developed in collaboration with Kitaoka Iron Works Co Ltd (Osaka, Japan) [14]. The polyethylene bag containing the resected nevus is then placed in the cavity of the cell of this HHP device and the cavity is filled with distilled water (Otsuka Pharmaceutical Co Ltd, Tokyo, Japan). The pressure is increased up to 200 MPa and maintained for 10 minutes, then decreased to atmospheric pressure over a period of a few seconds.

#### Retransplantation of the Inactivated Nevus

The pressurized and inactivated nevus is taken from the polyethylene bag and sutured to the original site. The nevus is fixed and stabilized to the wound bed using a tie-over dressing or negative pressure wound dressing for about one week after the retransplantation, as would be performed in a usual skin graft procedure. The graft is then covered by wound dressings or ointment gauze until the application of CEA. The inactivated nevus does not have any cellular components; however, within a few weeks fibroblasts and capillaries will infiltrate the nevus and the engrafted nevus will serve as an autologous dermis without nevus cells and will serve as a recipient floor for the CEA.

#### Preparation and Application of the CEA

A small section of the patient’s normal skin (approximately 1 cm × 2 cm) is taken from around the nevus region for the preparation of the CEA. This skin is transported to a laboratory and the CEA is prepared after a culturing process that usually takes three weeks. The CEA will be grafted on the engrafted inactivated nevus at four weeks after the retransplantation of the inactivated nevus.

#### Subsequent Therapy

The inactivated nevus and CEA is treated in the same way as a skin graft. The use of ointments and wound dressings are allowed locally and no particular restrictions will be imposed during the study period.

#### Digital Photography for the Assessment of Healing

A digital camera is used to capture images of the grafts with a calibrator (ColorChecker Passport, X-lite Inc, Michigan, United States) placed on the skin adjacent to the wound. The color and size of the images can be adjusted using the ColorChecker Passport and an image editing software program (Adobe Photoshop, Adobe Systems Inc) to assess the area and color of the target nevus. As with the primary endpoint, the nevus evaluation committee members will assess the original area of the nevus before its removal and the engrafted area of the pressurized nevus and epithelized area on the pressurized nevus at 8 weeks after transplantation of the CEA.

### Primary Endpoint

The primary endpoint is engraftment of the CEA at 8 weeks after its transplantation. The CEA is considered to be engrafted when the engraftment area of the inactivated nevus is 60% or more of the pretransplantation nevus area and 80% or more of the transplanted inactivated nevus is epithelialized. The proportion of the engraftment area is referred to as the engraftment rate. The engraftment assessment is carried out by three reviewers of the nevus evaluation committee. Macroscopic pictures of the grafts will be provided to each reviewer without patient information. The reviewers will determine the engraftment area of the inactivated nevus and the epithelized area based on these photographs.

With regard to the cutoff point of 60%, it has been reported that when autologous skin grafting is performed, the area of the skin graft contracts to approximately 80% at 3 months after grafting. Furthermore, in some cases the graft is reported to contract to approximately 60% [15]. We took the above information into consideration and set the cutoff point at 60% or more. Cases in which the engrafted area falls below 60% are not considered to be engrafted even if they are mostly epithelialized. Damage to the inactivated nevus by HHP may lead to such a degree of contracture.

When 80% or more of the CEA is epithelialized, it may be considered to be almost completely epithelized at the macroscopic level. Erosion and blister formation or shedding may occur in the early phase following grafting. The cutoff value for epithelialization was therefore set at 80% or more. This value takes the possibility of erosion and shedding, which may occur in some cases, into consideration [16].

### Secondary Endpoints

The event name, grade, and outcome of adverse events and adverse reactions will be assessed according to the Common Terminology Criteria for Adverse Events version 4.0. Adverse events and adverse reactions occurring from the day of the transplantation of the inactivated nevus until the end of follow-up will be assessed.

A secondary endpoint is engraftment of the inactivated nevus at 4 weeks after its transplantation. The inactivated nevus is considered to be engrafted when the pressurized nevus forms a successful recipient floor for the CEA.

### Blinding

The baseline nevus area before its removal, the engrafted area of the inactivated nevus, and the epithelized area 8 weeks after CEA transplantation will be independently estimated by blinding the members of the nevus evaluation committee. The patients will be unblinded, and the transplantation of the inactivated nevus and CEA will be performed by unblinded investigators.

### Sample Size

The target number of grafted sites of the inactivated nevus is 10 sites. In this study, one patient can receive the study treatment for up to 2 sites, thus a minimum of 5 patients will be included in this study.

The subjects of this study include pigmented nevus patients for whom primary closure is not expected. Regarding the number of newly diagnosed GCMN cases each year, few such cases are diagnosed at Kansai Medical University Hirakata Hospital, while approximately 5 cases are diagnosed at Kyoto University Hospital (which treats more cases). Considering the number of patients with a history of treatment for residual nevi and the need to include 10 sites (at least 5 cases), we determined that the enrollment period should be 1 year and 6 months.

### Study Schedule

The schedule of the study assessments and evaluations is shown in Figure 1. The study period will be from the day of informed consent to 12 weeks after the transplantation of the inactivated nevus. The data for evaluating the efficacy and safety of this study will be collected at enrollment, day 1, weeks 1 and 4 after transplantation of the inactivated nevus, and weeks 1 and 8 after the transplantation of the CEA.

**Figure 1 figure1:**
[figure not shown]
Schedule of the study assessments and evaluations.

### Statistical Analysis

When CEAs are transplanted on a wound bed without autologous dermal tissue, the engraftment rate is reported to be only 20%. In contrast, the engraftment rate is expected to be 80% when the CEA is transplanted on dermal tissue [17]. In this study, an engraftment rate of 80% can be expected because the autologous dermis is reconstructed using inactivated nevus tissue.

It was considered that the treatment could be deemed effective if it exceeds this engraftment rate. In this case, with an α error (one-sided) of .05 and a statistical power of 90%, the number of sites required was calculated to be 6 sites. Taking into consideration the possibility that some cases may be excluded from the analysis, we considered that there should be 10 target sites.

In our study, a single patient may undergo treatment for up to 2 sites. When two treatments are performed for the same patient, the first and second surgical sites are regarded as independent sites whether they are separated from each other by normal skin or nevus skin. Moreover, when providing simultaneous treatment to multiple sites in one subject, the largest treatment site will be included in the statistical analysis.

The incidences of adverse events and adverse events that can be causally related to the inactivated nevus and CEA application will be evaluated based on the event and severity. An interim analyses and auditing will not be planned; however, the investigators will monitor adverse events and other unintended effects of the trial interventions. A data monitoring committee consisting from three independent clinicians will also monitor patient safety and have the power to recommend termination of the study based on the evaluation of these results.

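### The effectiveness rule points to an 80% threshold, but the 6-site, 90%-power calculation only works as a test against 20%

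*Protocol article*

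**What the plan says.** All the relevant text is in the protocol article, Methods, Statistical Analysis. Two benchmark rates come first. For cultured epidermal autografts (CEA) on a bed lacking the patient's own dermis, "the engraftment rate is reported to be only 20" percent. By contrast, "the engraftment rate is expected to be 80% when the CEA is transplanted on dermal tissue". The plan then adopts the higher figure for this trial: "In this study, an engraftment rate of 80% can be expected because the autologous dermis is reconstructed using inactivated nevus tissue".

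The next sentence is the decision rule: "It was considered that the treatment could be deemed effective if it exceeds this engraftment rate". The sentence after that attaches the operating characteristics to the rule: "with an α error (one-sided) of .05 and a statistical power of 90" percent, "the number of sites required was calculated to be 6 sites". To allow for exclusions, "we considered that there should be 10 target sites".

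No null value is named anywhere in the article. The Design section says only that the take rate will be set against historical CEA data, and does not say which historical figure is meant.

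**The concern.** The last rate mentioned before the rule is 80%, so the rule makes 80% the bar. But 80% is also the rate the sponsor expects to achieve. A test whose null equals its expected value has no effect to detect, so it cannot have 90% power at 6 sites or at any other number. The decision rule and the power statement seem to belong to different hypotheses.

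The threshold decides what the trial may conclude. The study is small, open-label and single-arm, and an unresolved threshold could be settled after the results are known. There is also a risk of over-claiming: a result of 5 of 10 could be reported as effective to readers who understood the bar to be 80%.

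**Working it through.** **Inputs** (all from Statistical Analysis): candidate thresholds 0.20 and 0.80; expected rate 0.80; one-sided alpha 0.05; power 0.90; 6 required sites; 10 target sites. Sites are treated as independent, as the plan does. X is the number of engrafted sites out of n, binomial with success probability p.

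**1. Reproduce the 6 sites: null 0.20, alternative 0.80.** For each n, take the smallest r with P(X ≥ r | 0.20) ≤ 0.05; power is P(X ≥ r | 0.80).

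| n | r | alpha | power |
|---|---|---|---|
| 4 | 3 | 0.027 | 0.819 |
| 5 | 4 | 0.007 | 0.737 |
| 6 | 4 | 0.017 | 0.901 |
| 7 | 4 | 0.033 | 0.967 |
| 8 | 5 | 0.010 | 0.944 |
| 9 | 5 | 0.020 | 0.980 |
| 10 | 5 | 0.033 | 0.994 |

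For n = 6:
- alpha = 15(0.2⁴)(0.8²) + 6(0.2⁵)(0.8) + 0.2⁶ = 0.01536 + 0.00154 + 0.00006 = 0.0170
- power = 15(0.8⁴)(0.2²) + 6(0.8⁵)(0.2) + 0.8⁶ = 0.2458 + 0.3932 + 0.2621 = 0.9011

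Six is the first n to reach 90%, so the plan's figure is confirmed for 20% versus 80%. One-sided approximations with the same two rates give 3.8 (normal, so 4), 5.3 (continuity-corrected, so 6) and 5.2 (arcsine, so 6).

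**2. Threshold as the text reads: null 0.80, tested at one-sided .05.** The most extreme result possible is success at every site, with p-value 0.8ⁿ:
- n = 6: 0.8⁶ = 0.262
- n = 10: 0.8¹⁰ = 0.107
- n = 13: 0.8¹³ = 0.055
- n = 14: 0.8¹⁴ = 0.044

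No rejection region exists below 14 sites. The normal statistic agrees: (1 − 0.8)/√(0.16/n) is 1.22 at n = 6 and 1.58 at n = 10, both below 1.645. Since the expected rate equals this null, power cannot exceed alpha at any n. If the true rate were higher, 90% power against 80% would need 22, 44, 112 or 501 sites for true rates of 0.99, 0.95, 0.90 or 0.85. These rates are assumptions; the article gives none above 0.80.

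**3. Threshold as a point-estimate rule: observed proportion above 80%.** This needs at least 5 of 6 or 9 of 10. At a true rate of 0.80:
- n = 6: 6(0.8⁵)(0.2) + 0.8⁶ = 0.3932 + 0.2621 = 0.655
- n = 10: 10(0.8⁹)(0.2) + 0.8¹⁰ = 0.2684 + 0.1074 = 0.376

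Neither is near 0.90, and adding sites from 6 to 10 lowers the chance.

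**4. What 10 analysable sites would show.**

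| Engrafted sites | Test against 20% | Observed above 80% | Test against 80% |
|---|---|---|---|
| 0 to 4 | fail | fail | fail |
| 5 to 8 | pass | fail | fail |
| 9 or 10 | pass | pass | fail |

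At a true rate of 0.80, the chance of landing in the middle row is 0.994 − 0.376 = 0.618.

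**The case against.** The strongest reply is that the sponsor's own number settles the meaning. Only 20% versus 80% gives 6 sites; the 20% is worded as a reported figure and the 80% as an expectation; and the Design section promises a historical comparison. On this view there is a loose pronoun and nothing worse. The rule also does not say 'significantly', so calling it impossible to meet presupposes a test. The study is exploratory, and test details and critical counts usually belong in the analysis plan.

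Much of this is fair. Twenty percent was probably intended, and the figure of 6 is correct. The impossibility applies only to a one-sided .05 test; as a point estimate the rule can be met. But a reader has to reverse-engineer the calculation to recover 20%, against the order of the sentences. The Design section does not choose between the two rates, and both come from the same literature-based passage. The point-estimate reading also contradicts the stated power. Nor is this a missing detail left for another document: the article states a success criterion and follows it with a sample size that does not fit it. An exploratory aim does not remove the problem, because the article attaches alpha, power and a claim of effectiveness to that criterion.

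One caution stands. The Primary Endpoint section uses the term engraftment rate for a proportion of area, whereas a binomial calculation needs a proportion of sites. The match at 6 makes the per-site reading likely, but the corrected sentence should say so.

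**Conclusion.** The concern holds: the decision rule is wrong as written. Its natural threshold of 80% is incompatible with 6 sites and 90% power, whether it is read as a test (best possible p-value 0.262 at 6 sites and 0.107 at 10) or as an observed proportion (probability 0.655 and 0.376 at the expected rate). The sample size is sound for 20% versus 80%, with power 0.901 at 6 sites and 0.994 at 10. The error therefore lies in the threshold, not in the number of sites.

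This rests on three assumptions: that the rates are per-site proportions meeting the primary endpoint, that sites are independent, and that the test is exact binomial. The absence of any rejection region against 80% at 6 or 10 sites does not depend on the assumed true rate. It should be corrected before the data are analysed, because the threshold determines whether 5 to 8 successes out of 10 count as success.

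**What to change.** Replace the rule with wording such as: 'The treatment will be deemed effective if the proportion of sites meeting the primary endpoint is significantly greater than 20% (H0: p ≤ 0.20, exact binomial test, one-sided alpha .05). The planning alternative is p = 0.80.'

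Add the minimum number of successes for each analysable number of sites: 4 of 6, 4 of 7, 5 of 8, 5 of 9, 5 of 10. Each keeps alpha at or below 0.033 and power at or above 0.90 under p = 0.80. State that passing shows superiority to the 20% benchmark only, and does not show that 80% has been reached.

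If the sponsor did mean 80%, it should say so and withdraw the claim of 6 sites at 90% power, since neither 6 nor 10 sites can support that test.

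The cost of the recommended change is a short amendment to the protocol or analysis plan, with no additional patients or sites.

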### Ethics

This study is being conducted in compliance with the International Council for Harmonisation Good Clinical Practice and in accordance with the latest revision of the Declaration of Helsinki, Pharmaceutical Affairs Law and all applicable Japanese laws and regulations, as well all local laws and regulations and all applicable guidelines. This protocol and any amendments received Institutional Review Board (IRB) approval from Kansai Medical University (Approval number 1520-2).

